## Abstract

**Background:**

Early inhibition of entry and replication of the severe acute respiratory syndrome coronavirus 2 (SARS-CoV-2) is a very promising therapeutic approach. Polyclonal neutralizing antibodies offers many advantages such as providing immediate immunity, consequently blunting an early pro-inflammatory pathogenic endogenous antibody response and lack of drug-drug interactions.

By providing immediate immunity and inhibiting entry into cells, neutralizing antibody treatment is of interest for patient with COVID-19-induced moderate pneumonia. Convalescent plasma to treat infected patients is therefore a relevant therapeutic option currently under assessment (CORIMUNO-PLASM NCT04324047). However, the difficulties of collecting plasma on the long term are not adapted to a broad use across all populations.

New polyclonal humanized anti-SARS-CoV2 antibodies (XAV-19) developed by Xenothera and administered intravenous. XAV-19 is a heterologous swine glyco-humanized polyclonal antibody (GH-pAb) raised against the spike protein of SARS-CoV-2, blocking infection of ACE-2-positive human cells with SARS-CoV-2.

**Methods:**

Pharmacokinetic and pharmacodynamic studies have been performed in preclinical models including primates. A first human study with another fully representative GH-pAb from Xenothera is ongoing in recipients of a kidney graft. These studies indicated that 5 consecutive administrations of GH-pAbs can be safely performed in humans.

The objectives of this 2-step phase 2 randomized double-blinded, placebo-controlled study are to define the safety and the optimal XAV-19 dose to administrate to patients with SARS-CoV-2 induced moderate pneumonia, and to assess the clinical benefits of a selected dose of XAV-19 in this population.

**Discussion:**

This study will determine the clinical benefits of XAV-19 when administered to patients with SARS-CoV-2-induced moderate pneumonia. As a prerequisite, a first step of the study will define the safety and the dose of XAV-19 to be used.

Such treatment might become a new therapeutic option to provide an effective treatment for COVID-19 patients (possibly in combination with anti-viral and immunotherapies). Further studies could later evaluate such passive immunotherapy as a potential post-exposure prophylaxis.

**Trial registration:**

ClinicalTrials.gov NCT04453384, registered on 1 July 2020, and EUDRACT 2020-002574-27, registered 6 June 2020.

**Supplementary Information:**

The online version contains supplementary material available at 10.1186/s13063-021-05132-9.

## Administrative information

The order of the items has been modified to group similar items (see http://www.equator-network.org/reporting-guidelines/spirit-2013-statement-defining-standard-protocol-items-for-clinical-trials/).

**Role of sponsor {5c}**	All the submissions/declarations were made by the Sponsor Department at CHU Nantes, which of course manages the quality of the data collected. The data collected during the study will be processed electronically in accordance with the requirements of the CNIL, the French Data Protection Authority and with the European and French regulations regarding the safety concerns. Requests for substantial modifications of the protocol should be addressed by the sponsor for approval or notification to French regulatory authorities and/or the Ethical Review Board concerned in compliance with Law 2004-806 of 9 August, 2004 and its implementing decrees.

## Introduction

### Background and rationale{6a}

In December 2019, coronavirus disease 2019 (COVID-19) emerged in Wuhan, China. After10 months, COVID-19 causes more than 35,216,168 confirmed cases and more than 1,037,557 has been announced (https://coronavirus.jhu.edu/map.html viewed on 5 October 2020).

In the lack of effective therapy and without any control of the virus’ spread, the World Health Organization declared a public health emergency of international concern on 30 January 2020.

Severe acute respiratory syndrome coronavirus 2 (SARS-CoV-2) is a protein-enveloped RNA virus [1] that induces influenza-like symptoms (fever, cough, dyspnea, vomiting, diarrhea) requiring admission to hospital in 20% of cases for respiratory illnesses and to intensive care unit in 5% of cases for severe diseases [2]. Over 25% of patients develop acute respiratory distress during the second week of disease with the onset of severe acute respiratory distress syndrome (ARDS) [3].

SARS-CoV-2 infection has been reported to induce both direct organ damage [4, 5] and inappropriate immune response causing “viral sepsis” [6–8]. The pathophysiological mechanisms of severe infection are poorly understood [9]. In the most critical cases, the overwhelming immunological reactions induced by systemic multiorgan viral invasion lead to multiorgan failure and subsequent mortality [10]. It is likely that both antivirals and blockage of inflammatory pathways are needed to optimize responses.

Due to the urgent need to develop available therapies to manage the pulmonary complications of COVID-19, many efforts continue to develop antivirals and immunotherapies against COVID-19.

By providing immediate immunity and inhibiting entry into cells, convalescent plasma has been demonstrated to improve survival rate of patients with SARS-CoV infections in 2003 [11]. SARS-CoV-2 has been shown to use the same cell entry receptor as SARS-CoV, angiotensin-converting enzyme 2 (ACE2) [12, 13]. With the inhibition of SARS-CoV-2 spike glycoprotein (S)-mediated entry into cells, convalescent plasma is a promising approach to treat patients infected with SARS-CoV-2. Early administration of neutralizing Abs may inhibit viral entry and replication and consequently blunt an early pro-inflammatory response.

Xenothera, Nantes-based biotech company spin-off from the University of Nantes, has developed a novel polyclonal glyco-humanized (GH-pAb) anti-SARS-CoV2 swine antibody named “XAV-19”. GH-pAbs described by Vanhove et al. and Salama et al. [14, 15] have been evaluated for safety, pharmacokinetics, and pharmacodynamics effects in preclinical assessments in non-human primates and in volunteer kidney recipient patients dosed daily for 5 days at the five doses levels of 0.6 mg/kg, 1 mg/kg, 3 mg/kg, 6 mg/kg, and 8 mg/kg [16]. Forty milligrams per kilogram is therefore the maximal cumulative dose that has been administered in human. While the study is still ongoing, the Data and Safety Monitoring Committee (DSMC) agreed to pursue to the second segment of the study (therapeutic dose) where the GH-pAb will be administered 5 times at 8 mg/kg (cumulative dose of 40 mg/kg).

#### Efficacy of neutralizing antibodies (Abs)

In mice, neutralizing Ab against SARS-CoV elicited by primary infection can protect from secondary-infection and prevent SARS-CoV replication in respiratory tract of naïve mice [11]. Small retrospective case-comparisons studies in patients with SARS-CoV and SARS-CoV-2 suggested a case fatality rate reduction after convalescent plasma treatment [17–19]. An early administration at a time where pathology may be driven mainly by viral replication appears most suitable.

#### Safety profile

The issue of the potential toxicity associated with convalescent plasma and the difficulty in collecting it is a major limitation to the widespread use of this treatment. XAV-19 is a novel GH-pAb from Xenothera Laboratory technology. Per se, XAV-19 has never been administered in human. However, it is chemically comparable to LIS1, a lymphodepleting GH-pAb introduced in the clinic by Xenothera in 2019. LIS1 has been safely administered to kidney graft recipients at cumulated doses up to 40 mg/kg, representing 40-fold the lowest dose foreseen for XAV-19 in the POLYCOR study.

#### New polyclonal glyco-humanized anti-SARS-CoV2 antibodies formulation

The XAV-19 drug substance (DS) is a liquid, colorless, sterile solution concentrated at 5.0 ± 0.5 mg/mL. XAV-19 is generated as follows: the active substance manufacturing process starts from a pool of swine serum collected after immunization with a recombinant antigen (SARS-Cov-2 spike protein domain). The IgG fraction is being purified with a downstream process similar to processes used for mAb purification.

#### POLYCOR study

Knowing GH-pAbs are well tolerated in human and that neutralizing Abs can be an effective therapeutic approach during SARS disease, the POLYCOR aims to address, in randomized double-blinded, placebo-controlled study the efficacy of polyclonal humanized anti-SARS-CoV2 antibodies (XAV-19) in patients with COVID-19-induced moderate pneumonia.

POLYCOR is divided into 2 steps: the phase 2a will be a double ascending dose (DAD), double-blinded, placebo-controlled randomized study to select the optimal dose of XAV-19 for the phase 2b. The phase 2b (double fixed dose (DFD)) will be a double-blinded, placebo-controlled randomized study to assess clinical benefit and safety of the phase 2a selected dose of XAV-19 in 352 hospitalized adults with COVID-19-associated moderate pneumonia.

### Objectives {7}

#### The objectives of phase 2a study

The primary objectives are to (1) evaluate the titers of XAV-19 in treated patients versus placebo-treated patients at day 8 and (2) assess the safety and tolerability of XAV-19.

The secondary objectives of the study are to (1) characterize pharmacokinetics (PK) of XAV-19 infected patients over the time from D1 to D29, (2) evaluate the antibody titers of XAV-19 and to compare group 1 treated patients versus group 2 treated patients at day 8, and (3) describe groups of patients according to clinical variables (duration of supplemental oxygen, transfer in intensive care unit (ICU), normalization of fever, titer of biomarkers, ordinal scale assessed at day 15, hospital length of stay).

Exploratory objectives will be to assess the effects of neutralizing antibodies use on virus-induced immune response on longitudinal follow-up and to identify targets for “immuno-monitoring” for the next phase of the study and to investigate the immunogenicity of COVID-19 during treatment with XAV-19.

#### The objectives of phase 2b study

The primary objective of the study is to compare duration until weaning supplemental oxygen in the two groups of treatment before or at day 15.

The secondary objectives of the study are the comparison between two groups of:
Evolution of National Early Warning Score (NEWS 2) [20]Changes in the 7-point ordinal scale between baseline and day 15Improvement of one category from admission using the 7-point ordinal scaleNormalization of feverDuration of oxygen therapy over 29 daysOxygen requirement over 29 daysTime to weaning in supplemental oxygen and proportion without O2 requirement at D15Transfer to ICU with need for invasive mechanical ventilation or high flow O2Hospital length of stayAll cause of mortalitySafety of XAV-19

To note*,* two ancillary studies will complete the phase 2b. For the pharmacokinetic study, 16 patients will be included, as for the immuno-monitoring study 30 patients will be included. Analyses performed will be identical to those performed in the phase 2a study.

Study sites involved in these ancillary studies will propose to their first patients to participate to these studies. Patients can participate simultaneously to both studies.

The objective of the pharmacokinetic study is to characterize pharmacokinetics (PK) of XAV-19-infected patients over time from D1 to D29. Pharmacokinetic analysis corresponds to antibody titer measurements at day 1 (pre-dose, post-dose), day 3, day 5 (pre-dose, post-dose), day 8, day 15, and day 29.

Objectives will be to assess the effects of neutralizing antibodies use on virus-induced immune response on longitudinal follow-up and to identify targets for “immuno-monitoring” for the next phase of the study and to investigate the immunogenicity of COVID-19 during treatment with XAV-19.

### Trial design {8}

As already mentioned, POLYCOR is a phase 2 study with the aim to define the optimal XAV-19 dose to administrate to moderate COVID-19 patients and to evaluate its safety and efficacy. POLYCOR is divided in 2 steps. The phase 2a will be a double ascending dose (DAD), double-blinded, placebo-controlled randomized study to select the optimal dose of XAV-19 for the phase 2b. The phase 2b (double fixed dose, (DFD)) will be a double-blinded, placebo-controlled randomized study to assess clinical benefit and safety of the phase 2a selected dose of XAV-19 in 352 hospitalized adults with COVID-19-associated moderate pneumonia.

## Methods: participants, interventions and outcomes

### Study setting {9}

This study is multi-centered and national. The sixteen patients of phase 2a trial will be recruited in 4 hospitals, and more precisely in the Infectious Diseases Departments of University Hospital of Nantes, Lyon, Angers, and the Hospital of Saint-Antoine (Paris).

As soon as phase 2a is completed, phase 2b will begin with 31 hospital centers in addition to the 4 in phase 2a. These 35 centers will cover the entire national French territory.

### Eligibility criteria {10}

The population to be studied is adults (male or female), over 18 years old, hospitalized for COVID-19 infection confirmed by a positive RT-PCR of less than 10 days’ duration, associated with pneumonia and Sp02 ≥ 94% on oxygenotherapy. The patients will be recruited in the investigational sites declared on this study.

Women of childbearing potential (WOCBP) must use appropriate method(s) of contraception during the clinical trial (oral contraception, implant or intrauterine device (IUD). Pregnant women, women of childbearing potential (WOCBP) without effective contraception, women who are nursing, or patient under guardianship or trusteeship will not be included in the study. Furthermore, all sexually active male subjects must agree to use an adequate method of contraception throughout the study period and for 90 days after the last dose of study drug and agree to no sperm donation until the end of the study, or for 90 days after the last dose of XAV-19, whichever is longer.

The subjects cannot participate simultaneously in other interventional studies and until 3 months after the end of their participation to this study. All the inclusion and exclusion criteria are reported in Table 1.

**Table 1 Tab1:** Inclusion and exclusion criteria

Inclusion criteria	Exclusion criteria
❖ Male or female ≥18 years and ≤ 85 years	❖ Evidence of multiorgan failure (severe COVID-19)
❖ Women of childbearing potential (WOCBP) must use appropriate method(s) of contraception during the clinical trial (oral contraception, implant or IUD	❖ Mechanically ventilated (including ECMO)
❖ Willing and able to provide written informed consent prior to performing study procedures	❖ Receipt of immunoglobulins or any blood products in the past 30 days
❖ Hospitalized for COVID-19	❖ Psychiatric or cognitive illness or recreational drug/alcohol use that in the opinion of the investigator, would affect subject safety and/or compliance
❖ Positive SARS-CoV-2 RT-PCR in any body specimen (nasopharynx, saliva, sputum) ≤ 10 days before enrolment	❖ End-stage renal disease (eGFR < 15 ml/min/1,73 m^2^)
❖ Evidence of pulmonary involvement (on lung examination [rales/crackles] and/or chest-imaging [Chest X-ray or computed tomography])	❖ Child-Pugh C stage liver cirrhosis
❖ Requiring O2 supplement ≤6 L/min at screening	❖ Decompensated cardiac insufficiency
❖ Requiring O2 supplementation with SpO2 ≥ 94% on O2 therapy at screening	❖ **History of active drug abuse**
❖ First onset of COVID-19 symptoms ≤10 days, among fever and/or chills, headache, myalgias, cough, shortness of breath, whichever as occurred fist	❖ Known allergy, hypersensitivity, or intolerance to the study drug, or to any of its components
❖ WOCBP must have a negative urinary pregnancy test the day of inclusion	❖ WOCBP without contraceptive method, or with positive pregnancy test, breastfeeding, or planning to become pregnant during the study period
❖ All sexually active male subjects must agree to use an adequate method of contraception throughout the study period and for 90 days after the last dose of study drug and agree to no sperm donation until the end of the study, or for 90 days after the last dose of XAV-19, whichever is longer	❖ Current documented and uncontrolled bacterial infection
❖ Patients with French social security	❖ Prior severe (grade 3) allergic reactions to plasma transfusion
	❖ Patient participating in another interventional clinical trial
	❖ Life expectancy estimated to be less than 6 months
	❖ Patient under guardianship or trusteeship

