The primary endpoint of the phase 2b is the time to weaning of supplemental oxygen.

If patient is still on oxygen at day 15 or if the patient is weaned but put back on oxygen, then the delay will be censored at 15 days.

The secondary endpoints are the:

National Early Warning Score (NEWS2) at day 15 and difference in NEWS2 between day 1 and day 15Clinical status using the 7-point ordinal scale assessed at day 3, day 5, day 8, day 11, day 15, and day 29Time to improvement of one category from admission using the 7-point ordinal scaleTime to first fever normalization (criteria for normalization: temperature < 36.6 °C armpit, < 37.2 °C oral, < 37.8 °C rectal or tympanic)Duration of oxygen therapy over 29 daysComparison of oxygen requirement between the two groups over 29 daysTime to weaning in supplemental oxygen and proportion without O2 requirement at day 15, according to baseline (day 1) oxygen requirement (≤ 4 L/min or 4 L/min)Incidence and duration of non-invasive ventilation or high flow oxygen devices, of invasive mechanical ventilation during the studyHospital length of stayAll-cause mortality at Day 29Safety of XAV-19 evaluated as:Occurrence of all suspected XAV-19-related adverse effects or incidence of serious adverse eventsProportion of participants with treatment emergent adverse events leading to study drug discontinuationIncidence of major or opportunistic bacterial or fungal infectionsIncidence of hypersensitivity reactions and infusion reactionsWhite cell count, hemoglobin, platelets, creatinine, ALT, AST, on day 1, day 3, day 5, day 8, day 11, day 15, and day 29SARS-CoV-2 viral load over time (day 1–day 29), as collected by nasopharyngeal swab samplesTime to RT-PCR virus negativity in nasopharyngeal swab samples

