### Sample size {14}

As it is a phase 2a, the number of patients was determined according to phase 2a’s relevant publications [23–25] . It was decided to enroll two cohorts of 8 patients (6 treated patients and 2 matching placebo in each cohort).

For the phase 2b, the predetermined sample size, controlling for the α risk of 5% and power of 80%, is 352 participants, based on an expected survival rate of patients giving up oxygen therapy at least at day 15 of 80% in the control group and 90% in the experimental group. In addition, the median duration of oxygen therapy in the control group is 8 days, and in the experimental group is 6 days. Hence the estimated hazard ratio is 0.75. The sample size was calculated following the formula of Schoenfeld [26] and the hazard ratio was estimated thanks to Cortes’ publication [27].

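### Patients on long-term oxygen before COVID-19 can be enrolled although, read literally, they cannot be weaned; this dilutes the phase 2b primary comparison by an unknown, probably modest, amount

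*Protocol article*

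**What the plan says.** All of this is in the protocol article.

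- **Eligibility criteria {10}.** Two lines of Table 1 concern oxygen: "Requiring O2 supplement ≤6 L/min at screening" and "Requiring O2 supplementation with SpO2 ≥ 94% on O2 therapy at screening". Neither says that the need must be new or due to COVID-19. The exclusions name end-stage renal disease, Child-Pugh C cirrhosis, decompensated cardiac insufficiency, mechanical ventilation and a life expectancy below 6 months. They do not name chronic respiratory failure or home oxygen. The section also states: "All the inclusion and exclusion criteria are reported in Table 1".
- **Outcomes {12}.** "The primary endpoint of the phase 2b is the time to weaning of supplemental oxygen". The rule for patients without the event begins "If patient is still on oxygen at day 15 or if the patient is weaned but put back on oxygen" and censors them at 15 days. Return to a pre-existing oxygen flow is not mentioned.
- **Sample size {14}.** The target, "controlling for the α risk of 5% and power of 80%, is 352 participants", rests on day-15 weaning "of 80% in the control group and 90% in the experimental group", on median oxygen durations of 8 and 6 days, and on a hazard ratio of 0.75 in Schoenfeld's formula.

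**The concern.** Take a patient with stable lung disease who uses oxygen at home and is admitted with COVID-19 pneumonia on a higher flow, still at most 6 L/min, with saturation of at least 94%. The patient can satisfy Table 1. After full recovery from COVID-19, the patient goes back to the usual home oxygen and is still on oxygen at day 15. The endpoint as worded records that recovery in the same way as a failure to improve, whichever treatment was given.

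Such patients stay in the risk set to day 15 without being able to contribute an event. In a log-rank comparison this pulls the observed hazard ratio towards 1. Two secondary endpoints, oxygen duration over 29 days and the proportion off oxygen at day 15, are affected in the same way. The planned split by baseline flow at 4 L/min does not identify these patients.

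**Working it through.** **1. The plan's own figure.** Inputs from Sample size {14}: HR 0.75, alpha 5%, power 80%, weaned by day 15 80% and 90% (mean 85%). Allocation is 1:1.

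Schoenfeld events: D = 4(z₁₋α + z₁₋β)² / (ln HR)².

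- One-sided 5%: 4 × (1.645 + 0.842)² / 0.0828 gives 299 events. 299 / 0.85 = 351.8, so N = 352, which matches exactly.
- Two-sided 5%: 380 events. 380 / 0.85 gives N = 448, which does not match.

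The stated N is therefore reproduced at one-sided 5%, with no inflation. One-sided power is used below for that reason.

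**2. Lost events only.** Let f be the share of patients who cannot be weaned, equal in both arms. The documents do not give f, so 1%, 2% and 5% are assumptions.

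D(f) = 352 × 0.85 × (1 − f), and power = Φ(√D × |ln 0.75| / 2 − 1.645).

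| f | Events | One-sided power |
|---|---|---|
| 0 | 299 | 0.800 |
| 1% | 296 | 0.797 |
| 2% | 293 | 0.793 |
| 5% | 284 | 0.782 |

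This understates the loss, because it keeps the hazard ratio at 0.75.

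**3. With dilution.** This is a log-rank simulation with 176 per arm, exponential weaning times and cut-off at day 15. A share f in each arm never has the event. Replicate runs agree to within about 0.01 to 0.02.

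- *A: HR 0.75, f added on top of the 20% of controls not weaned.* Control hazard −ln(0.20)/15; treated hazard is that divided by 0.75.
- *B: HR 0.75, f already inside that 20%.* Control hazard −ln(1 − 0.80/(1 − f))/15; treated hazard is that divided by 0.75.
- *C: weaning rates of 80% and 90% among weanable patients, f on top.* Hazards −ln(0.20)/15 and −ln(0.10)/15, which imply HR = ln 0.20 / ln 0.10 = 0.70.

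| f | A: events | A: power | B: events | B: power | C: power |
|---|---|---|---|---|---|
| 0 | 296 | 0.80 | 296 | 0.80 | 0.92–0.93 |
| 1% | 293 | 0.78 | 296 | 0.78 | 0.92 |
| 2% | 290 | 0.76 | 295 | 0.76–0.77 | 0.90–0.91 |
| 5% | 281 | 0.70 | 294 | 0.70–0.72 | 0.86 |

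A and B lose about the same power although B loses almost no events, so the loss comes mainly from dilution of the hazard ratio. In a fourth setting, the 80% and 90% hold for the whole enrolled population with f inside them. Events then stay at 299 and power does not fall, because a fixed overall difference implies a larger effect among weanable patients.

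**The case against.** Several objections have force.

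- **The share is unknown.** No document gives it, and admission for COVID-19, the 6 L/min ceiling, the saturation floor, the age limit of 85 and the life-expectancy criterion all narrow the group. This stands: the loss is conditional, and at 1% it is about 2 points at HR 0.75.
- **The endpoint wording may be completed elsewhere.** An article condenses the protocol, and the full document may define weaning for patients with prior oxygen. This stands in part. It means these patients are not certain non-events; they are so only if weaning means no oxygen at all, which the article does not spell out. It does not answer the eligibility gap, because the article declares its criteria list complete.
- **The plan already expects non-weaned patients.** A reader might infer that the sample size presumes everyone can come off oxygen. It does not: 20% of controls and 10% of treated patients are assumed still on oxygen at day 15, and some may be long-term users. Setting B shows that the loss at HR 0.75 remains even so, but the fourth setting shows none.
- **Bias.** A reader might infer that the result could be tilted. Randomisation is 1:1 and double-blind, so neither arm is favoured systematically. Chance imbalance is possible, as with any prognostic factor.
- **Two-sided power.** At two-sided 5% and HR 0.75, power is already about 0.70 with no such patients. That gap of 10 points concerns the sidedness of the sample-size calculation and should not be attributed to home oxygen.

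**Conclusion.** The gap holds on the text: the declared-complete criteria admit prior long-term oxygen users, and the primary endpoint as worded gives them no way to have the event. The consequence is a diluted effect and lower power, with neither arm favoured.

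The size cannot be fixed from the documents. At HR 0.75 the cost is about 2, 4 and 10 points of one-sided power for assumed shares of 1%, 2% and 5%. Under the 80% and 90% rates, power remains at about 0.86 or more over that range. These figures assume exponential weaning times and an equal share in both arms. The documents do not support calling this a serious loss of power or a reduction in events by a known number. It is a point to consider.

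**What to change.** Choose one of two changes:

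1. Add to the exclusions in Table 1: *long-term (home) oxygen therapy before the current COVID-19 episode*.
2. State in the primary endpoint that, for patients on long-term oxygen before COVID-19, weaning means return to their pre-COVID oxygen use.

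Trial status says that phase 2b began in January 2021, so some such patients may already be randomised. For them, add a sensitivity analysis of the primary endpoint that leaves them out. The group is defined by a baseline characteristic, so the analysis introduces no post-randomisation selection.

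The first change costs a line in an amendment, a small number of screened patients, and results that no longer cover people on home oxygen. The second keeps the population but needs the usual oxygen use recorded at baseline.
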